## 4 Conclusions

The study endeavors to assess biomarkers as predictive indicators for the relapse or remission of MDD, with the overarching goals of advancing digital technologies in predicting psychopathological severity, evaluating treatment efficacy, distinguishing individuals with MDD, and forecasting psychopathology severity through digital biomarkers. Simultaneously, this study seeks to validate an AI tool for early MDD diagnosis, implement an AI solution for continuous data processing, and establish an AI infrastructure for healthcare Big Data management. The integration of innovative psychophysical assessment tools in clinical practice is pivotal, aiming to enhance diagnostic efficiency and develop more specific digital devices for comprehensive mental health evaluation.

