**Conclusion:**

This study seeks to validate an AI tool for enhancing early MDD clinical management, implement an AI solution for continuous data processing, and establish an AI infrastructure for managing healthcare Big Data. Integrating innovative psychophysical assessment tools into clinical practice holds significant promise for improving diagnostic accuracy and developing more specific digital devices for comprehensive mental health evaluation.

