### 1.5 Aim of the study

This study focuses on evaluating specific digital and environmental biomarkers in adolescents and young adults diagnosed with MDD. The study, conducted through a prospective investigation on the MDD population (i.e., MDD), aims to:

Evaluate digital, environmental, and blood biomarkers as predictive indices of recurrence or remission of depressive pathology.Enhance digital technologies useful for predicting the severity of psychopathology and assessing treatment effectiveness.Apply technologies to distinguish individuals with depression and determine a personalized approach.Predict the severity of psychopathology among subjects using biomarkers derived from digital tools.

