**Figure 2 F2:**
[figure not shown]
Master data platform.

The experimental sample included 80 subjects aged 14 to 50 diagnosed with MDD (after administration of SCID-5 CV) who have been on stable medication for at least 16 weeks.

To achieve a 95% confidence level with a 5% margin of error in statistical sampling, considering a population proportion of approximately 50% and a known population size constituting 80% of the total, a minimum of 67 patients will be required. This calculation incorporates factors like the Z-score, standard deviation, and a finite population correction for larger populations. The meticulous consideration of these elements ensures the reliability and precision of the sample size, thus enhancing the credibility of the statistical findings in representing the broader population.

Participants will be excluded if they presented: intellectual disability; current or previously diagnosed psychotic disorder; mood disorder with psychotic features; bipolar disorder; alcohol and drug use with psychotropic effects according to DSM-5; pathologies of a chronic inflammatory nature; history of gastrointestinal disorders in the previous week; pregnancy.

The sample will be divided into two age groups (14–17 years and 18–49 years) and distributed in a randomized manner by random allocation in two different groups (group A and group B), each consisting of 40 subjects (10 adolescents and 30 adults).

Based on data from the Italian Statistical Institute (ISTAT) regarding the incidence of depression among italian adolescents, 20 teenager were included in the total sample.

Only the subjects assigned to group B will receive the technological equipment (Pothos system and smartwatch) for the collection of digital biomarkers; group A will be followed according to clinical standards of care. Specialized medical personnel will follow both groups from a pharmacological point of view.

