The assessment will include socio-demographic information, clinical history, medication details, and various clinical scales for evaluating depression severity (HAM-D, MADRS, CDI-2) and overall functioning (GAF, C-GAS, CBCL 6–18). Clinical parameters that will be monitored daily include: heart rate, and respiratory rate, oxygen saturation, light intensity, sleep/wake rhythm, and daily step count. The daily mood will be detected by using specific emoticons by the study participants. Additionally, vocal analysis will be conducted weekly using an “*ad hoc*” app to evaluate global articulation rate, fundamental frequency, and energy during specific tasks. Specific characteristics to be analyzed include F0 range (Hz), Energy per second (mV2), Average pause duration (s), Total pause time (s), and Variability of pauses (s).

The study will also include the collection of blood and saliva samples to assess inflammatory biomarkers (IL-1β, IL-2, IL-4, IL-5, IL-6, IL-10, IL-12, and IFNγ) and cortisol levels at the beginning (T0) and the end of the study (T1). Samples of peripheral blood and saliva will be taken in the group of patients with MDD and controls.

Blood withdrawal is necessary to recover the plasma and dose cytokines of pro- and anti-inflammatory cascade; the salivary sample allows the dosage of cortisol instead. Blood (7 ml) will be collected in K_2_-EDTA tubes, and plasma will be obtained through a density gradient centrifugation using SepMate™ Tubes. According to the manufacturer's instruction, blood will be diluted with PBS and then stratified on a gradient density medium (LymphoSep™, Biowest) that will allow the separation of plasma and other components after centrifugation at 1,200 × g for 10 min at a room temperature, brake on. Plasma will be recovered and stored at −80°C until it is used.

Saliva (>1 ml) will be collected in the morning, before brushing teeth and consuming food, through the use of a Salivette^®^ (Sarstedt), a test tube containing a swab to be chewed slowly for 2 min. Salivette^®^ will be centrifuged at 1,500 × g for 10 min at 4°C and then saliva will be recovered and stored at −20°C until the use.

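### The Conclusions promise validation of an AI tool for early MDD diagnosis, but everyone in the defined sample already has treated MDD and no defined non-MDD participant supplies device data

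*Protocol article*

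**What the plan says.** **The claim.** Section 4 (Conclusions) says that "this study seeks to validate an AI tool for early MDD diagnosis". The same section lists telling apart people with MDD among its overarching goals and speaks of more efficient diagnosis. The Conclusion of the Abstract words the AI goal differently, as to "validate an AI tool for enhancing early MDD clinical management", but then also refers to better diagnostic accuracy. The deep-learning paragraph of section 2 (Methods) names improved diagnosis as something the platform should help with. Section 1.5 lists the aim "Apply technologies to distinguish individuals with depression and determine a personalized approach".

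**The sample.** Section 2, in the text after Figure 2, describes "80 subjects aged 14 to 50 diagnosed with MDD (after administration of SCID-5 CV) who have been on stable medication for at least 16 weeks". These 80 are randomised to groups A and B, with 40 in each (10 adolescents and 30 adults). Only group B receives the Pothos system and smartwatch for collecting digital biomarkers. Group A is followed under standard care.

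**The controls.** The sampling paragraph of section 2 says: "Samples of peripheral blood and saliva will be taken in the group of patients with MDD and controls". The article does not mention controls as a study group anywhere else.

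**The classification.** Section 3 (Results) classifies participants at 6 months by remission, defined as HAM-D ≤ 7.

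**The concern.** Validating a diagnostic tool means showing that it separates people who have the condition from people who do not. That needs both kinds of participant, measured with the tool. Here the defined sample contains one kind only, and the device data come from half of it.

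The word early adds a second difficulty. A tool for early diagnosis would be used in people whose diagnosis is not yet made. These participants are already diagnosed and have been treated for at least 16 weeks.

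What is at stake is the reading of the result. The design can show whether biomarkers separate remitted from non-remitted patients. If the diagnostic goal stays in the text, such a finding could be taken as evidence that the tool diagnoses MDD, which it would not be.

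**Working it through.** **1. Inputs (section 2, text after Figure 2)**

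| Quantity | With MDD | Defined without MDD |
|---|---|---|
| Enrolled | 80 | 0 |
| Group A (standard care) | 40 | 0 |
| Group B (Pothos and smartwatch) | 40 | 0 |

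**2. The plan's own figure.** The article requires at least 67 patients for 95% confidence and a 5% margin at a proportion of 50%.

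- n0 = z² p(1 − p)/e² = 1.96² × 0.25/0.05² = 384.1.
- With a finite population correction, n = n0/[1 + (n0 − 1)/N].
- The article gives no clear N. Taking N = 80, the trial's own sample, is an assumption. It gives 384.1/(1 + 383.1/80) = 66.4, rounded up to 67.
- N = 64 gives 55.0 and N = 100 gives 79.5. Neither reproduces 67.

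So 67 is reproduced as the precision of a single proportion. It says nothing about diagnostic accuracy.

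**3. What can be estimated for MDD versus no MDD**

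- Sensitivity = true positives / number with MDD. The denominator is 40.
- Specificity = true negatives / number without MDD. The denominator is 0, so it is undefined.
- The false-positive rate, the likelihood ratios and the AUC all need the non-MDD group and are undefined too.

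The article does not say explicitly which group uses the voice and mood app. If all 80 supplied those data, the sensitivity denominator would rise to 80, but the specificity denominator would still be 0.

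**4. Precision of sensitivity alone.** The 95% half-width is 1.96 × √[p(1 − p)/n]. The article gives no accuracy values, so p is assumed.

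| Assumed sensitivity | n = 40 | n = 80 |
|---|---|---|
| 0.7 | ±0.142 | ±0.100 |
| 0.8 | ±0.124 | ±0.088 |
| 0.9 | ±0.093 | ±0.066 |

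Precision is not the main problem. With no non-cases, a rule that calls everyone depressed has 100% sensitivity.

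**5. What a diagnostic aim would need.** For a half-width of ±0.10 on specificity, n = 1.96² × p(1 − p)/0.10². This is 81, 62 or 35 non-MDD participants with device data at an assumed specificity of 0.7, 0.8 or 0.9.

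**6. The two readings of the controls**

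- If they are group A, they have MDD and cannot serve as non-cases.
- If they are a separate non-MDD group, they lie outside the 80 and outside the two-group allocation. Their number and eligibility are not given, and the article assigns them only blood and saliva sampling.

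Under either reading, the count of defined non-MDD participants with device data stays at 0.

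**The case against.** **Controls may exist.** A reader might infer that the trial has no control group at all. The article does not support that. It mentions controls once, it calls the 80 the experimental sample, and a condensed article may omit a group that the full protocol defines. This stands. What can be said is that the controls are undefined here, do not fit the stated sample and allocation, and are given no devices.

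**The aim in section 1.5 is ambiguous.** A reader might infer that this aim fails as well. That section describes an investigation of the MDD population, so distinguishing individuals can mean stratifying among depressed patients, which an all-MDD sample allows. This stands. The wording needs clarifying but is not shown to be unanswerable. The same reading does not rescue the early-diagnosis goal in section 4.

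**Some discrimination is possible.** A reader might infer that the data can say nothing about early signs of illness. Section 3 separates remitted from non-remitted patients, so specificity for that contrast has a non-zero denominator if some patients remit. This stands, but it concerns prognosis or current state within MDD. The zero denominator applies to MDD versus no MDD.

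**Misreporting is not planned.** The article describes no diagnostic-accuracy analysis, so a false claim of validation is a risk and not a stated intention. A device-based contrast of A with B could not arise, because only B has the devices.

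**The contrast between Abstract and Conclusions is not clean.** The Abstract speaks of clinical management but also of diagnostic accuracy. Copying its phrase would therefore not resolve the matter, and that phrase also keeps the reference to early MDD.

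**Conclusion.** The point holds for the early-diagnosis goal in section 4. As the sample is defined, device data come from 40 people with treated MDD and from 0 defined people without MDD. Specificity, AUC and likelihood ratios for MDD versus no MDD cannot be estimated, and sensitivity on 40 cases does not validate a diagnostic tool. This follows from who is enrolled and who receives devices, so it is not a detail that an analysis plan could settle.

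The conclusion rests on the Methods being complete as to who receives the Pothos system and smartwatch. It would change only if the full protocol defined a non-MDD or suspected-MDD group with device data. The half-widths and control numbers rest on assumed accuracy values.

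The correction should be made, but it is not critical. The first-listed aim, prediction of recurrence or remission, is untouched, and the remedy is a matter of wording.

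**What to change.** 1. **Section 4.** Replace the diagnosis-validation goal with what the sample supports: predicting remission (HAM-D ≤ 7), recurrence and symptom severity within treated MDD, using the device data of group B.
2. **Related statements.** Apply the same limit to the goal of telling apart people with MDD and the remark on diagnostic efficiency (both section 4), the remark on diagnostic accuracy (Conclusion of the Abstract), and the remark on improving diagnosis (deep-learning paragraph, section 2).
3. **Section 1.5.** State that distinguishing individuals means stratification within MDD.
4. **Sampling paragraph, section 2.** Reconcile the controls with the sample description by stating whether they are group A or a separate non-MDD group. The sponsor has to supply the answer. Rewording the sentence to mean groups A and B without checking could delete a real design element.

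The cost is a narrower claim, with no added patients, visits or assays.

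If the sponsor wishes to keep the diagnostic goal, wording is not enough. The plan would have to define non-MDD or suspected-MDD participants with device data, and a sample size for sensitivity and specificity. As a guide, 35 to 81 non-MDD participants would give ±0.10 on specificity over the assumed range of 0.9 down to 0.7. A claim about early diagnosis would also need people who are not yet diagnosed.

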## Ethics statement

The study protocol and informed consent form have been approved by the Campania Sud Review Board (Application no. 48_r.p.s.o.).
